Although neuromuscular training exercise and taping are recommended treatments for PFPS patients, their effectiveness still remains disputed. On the one hand, several studies proved that neuromuscular training exercise and taping have positive effects in the treatment of PFPS, especially in improving muscle strength and knee joint proprioception sense ability [12, 16]. The scholar Hande Guney reported that quadriceps strength and joint position sense are strongly correlated with pain and knee function in PFPS patients [20]. On the other hand, several studies proved that these treatments may not be efficacious in improving the muscle strength or joint position sense ability of patients with PFPS [21, 22] and joint position sense may not have any difference between PFPS patients and normal individuals [23].

The objective of the present study is to determine whether neuromuscular exercise training and taping are effective in improving knee function and lessening the pain in PFPS patients. Thus, we will design a single-blind randomized controlled trial (RCT). Compared with other studies, we will ask individuals to follow several muscle strength-training regimens, including quadriceps femoris and gluteus strength training, especially the medial vastus muscle. Moreover, we will use a balance pad to train the balance ability and CON-TREX multijoint isokinetic test and training machine to train the patients’ knee proprioception sense ability.

According to previous studies, health education is important among people who suffered from PFPS [24–26]. As a result, we set up a control group named “health education;” the control group will be used to compare with the other two groups. In addition, the health education program contents are as follows: it will give the participants publicizing and knowledge about how to protect the knee from injury while they are running or in the daily life as well as the concept of PFPS and self-management strategies on it.

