### Hypothesis

The neuromuscular training exercise and taping both have a positive effect on the treatment of PFPS.The neuromuscular training exercise has a higher advantage than taping and health education in treating PFPS patients.

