### Participants

#### Inclusion and exclusion criteria

The participants should meet the following requirements: (1) aged 20–50 years; (2) running more than half a year and pain lasting longer than one month; (3) anterior or retropatellar knee pain from at least two of the following: prolonged sitting; climbing stairs; squatting; running; kneeling; and hopping/jumping; (4) anterior knee pain is not caused by trauma; (5) the patellofemoral joint extrusion test is positive. The exclusion criteria are as follows: (1) meniscus injury; (2) laxity of articular ligament; (3) pressure pain on the tibial tract, the goose foot tendon, and patellar ligament; (4) effusion of knee joint; (5) history of patellar dislocation; (6) severe cardiovascular or osteoporosis, progressive neurological deficits; (7) pregnancy women or lactating women; (8) VAS score (in the range of 1–10) > 8; and (9) VAS score (in the range of 1–10) < 3.

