### Statistical analysis

Statistical analyses will be carried out using SPSS 22.0 and Microsoft Excel 2012 software. Data will be represented as mean ± standard deviation. We will use two-way repeated measures analysis of variance (group × time) to compare the effect of neuromuscular training exercise group with the taping and control groups, including the primary and secondary outcomes. The intention-to-treat analysis will be conducted if individuals are lost to follow-up. The t-test will be carried out to compare the changes in measures within groups. Statistical significance will be considered at *P* value < 0.05.

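### No taping versus health education comparison is named, so taping's hypothesised effect rests on within-group t-tests that can be significant without any treatment effect

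*Protocol article*

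**What the plan says.** Three places in the protocol article bear on this.

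- **Hypothesis.** There are two claims. The first is about each active treatment: "The neuromuscular training exercise and taping both have a positive effect on the treatment of PFPS". The second is about superiority: "The neuromuscular training exercise has a higher advantage than taping and health education in treating PFPS patients".
- **Background.** The objective is to "determine whether neuromuscular exercise training and taping are effective in improving knee function and lessening the pain in PFPS patients". On the health education arm it says that "the control group will be used to compare with the other two groups".
- **Statistical analysis.** The two-way repeated measures ANOVA (group × time), for primary and secondary outcomes, is there "to compare the effect of neuromuscular training exercise group with the taping and control groups". A second analysis follows: "The t-test will be carried out to compare the changes in measures within groups". The section closes with one significance rule: "Statistical significance will be considered at" P < 0.05. That rule is not confined to the ANOVA, so the t-tests are stated as inference and not as description.

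Patients are also selected on a primary outcome. The Inclusion and exclusion criteria exclude a VAS above 8 and, as the last exclusion, a "VAS score (in the range of 1–10) < 3".

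**The concern.** The Background gives the education arm the role of comparator for both active arms. The Statistical analysis section carries this through for training only. For taping, the named between-group contrast is with training, and no contrast with education is named. The one named analysis left that bears on whether taping has a positive effect is the change within the taping arm.

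That test does not use the randomised control. A fall in VAS or a rise in AKPS over three or six months can come from natural recovery, from attention and expectation, or from regression to the mean after selection on VAS. A within-arm t-test counts all of these together with any treatment effect. At stake is a statement that taping is effective, and possibly that training is effective, resting on evidence that would look the same if neither did anything. The education arm could also show a significant improvement on the same test.

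**Working it through.** **1. Hypotheses set against named analyses.**

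| Question | Randomised comparison named in Statistical analysis | Within-group t-test |
|---|---|---|
| Training has a positive effect | Yes: training vs control, in the ANOVA's stated purpose | Yes |
| Taping has a positive effect | None named | Yes |
| Training better than taping and education | Yes, in the ANOVA's stated purpose | Not applicable |

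The gap is the second row.

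**2. Inputs.** From the article: 20 patients per group (Sample size estimation), P < 0.05 (Statistical analysis), entry VAS 3 to 8 (Inclusion and exclusion criteria). Assumed: two-sided testing, the correlation ρ between baseline and follow-up, and the size of any change that is not due to treatment. The article gives no figure for how often the within-group tests would reject, so there is none to reproduce.

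**3. Within-arm t-test with zero treatment effect.** Let every arm improve by d standard deviations for reasons other than treatment, with equal SD at both visits. The standardised mean change is d_z = d / √(2(1 − ρ)). The noncentrality is d_z × √20, with 19 degrees of freedom and critical value 2.093. Example: d = 0.5 and ρ = 0.5 give d_z = 0.5 / √1 = 0.5, noncentrality 0.5 × 4.472 = 2.236, and probability 0.564 of a significant improvement.

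| Common non-treatment improvement | ρ = 0.3 | ρ = 0.5 | ρ = 0.7 |
|---|---|---|---|
| 0 | 2.5% | 2.5% | 2.5% |
| 0.2 SD | 10.7% | 13.3% | 19.4% |
| 0.5 SD | 43.4% | 56.4% | 78.2% |
| 0.8 SD | 81.8% | 92.4% | 99.2% |

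**4. Regression to the mean through the VAS entry window.** This was simulated with three arms of 20, no treatment effect, baseline VAS kept between 3 and 8, assumed SD 2 and ρ 0.5–0.7. The result depends on the assumed mean VAS in the population from which patients are drawn.

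| Assumed source mean VAS | Mean fall, selection alone (points) | Arms with significant improvement |
|---|---|---|
| 2 | 0.67–1.10 | 51–76% |
| 3 | 0.46–0.76 | 27–44% |
| 4 | 0.27–0.44 | 12–18% |
| 5 | 0.09–0.15 | 4–5% |
| 6 | −0.14 to −0.08 (a slight rise) | about 1% |

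Adding an assumed natural improvement of 1 VAS point to every arm moves the rate to 51–99.9% over the same range of means and correlations.

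**5. The same simulated data, compared between arms.** A two-sample t-test of change between one active arm and education, and a three-group F-test of change, rejected in 4.7–5.2% of trials in every scenario. A change shared by all arms cancels in the randomised comparison. It does not cancel within an arm.

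**The case against.** The strongest reply is that the plan already has a randomised analysis. The group × time ANOVA compares training with control, so the t-tests are not the only analysis of whether training is effective. The three-group interaction also contains the taping and education data, and the Background shows that a comparison of those two arms is intended. Contrasts after an omnibus test are often left to a statistical analysis plan. No sentence ties the t-tests to the first hypothesis or makes within-group significance a rule for success. The t-tests need not mislead either: with little change over time they are significant in only 1–5% of arms. Because VAS above 8 is also excluded, selection can even push the mean slightly upward.

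Most of this stands, and it limits the point. A reader might infer that the whole effectiveness claim rests on before-after tests, or that such tests will show improvement when treatments do nothing. The documents support neither reading. The first fails for training because the ANOVA names training versus control. The second turns a possibility into a certainty. Nor do they support a count of false positives across all measures and visits, because the article does not say that every measure is t-tested at every visit.

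One part does not stand. The article does not leave the contrasts open. It states the ANOVA's purpose, and that statement omits taping versus education. A significant three-group interaction would not by itself show that taping differs from education. The choice of an uncontrolled test judged at P < 0.05 is also stated, not deferred.

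**Conclusion.** The point holds in a limited form. The Statistical analysis section names no taping versus health education comparison, although the Background and the first hypothesis call for one. The within-group t-tests are then the only named analysis that speaks to taping's effect, and they could also be cited for training. Linking them to the first hypothesis is an inference from how the sections fit together, not something the article says.

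The size cannot be fixed from the article, which gives no VAS standard deviation, correlation, source population mean or natural course. Under the assumptions shown, with no treatment effect, the chance that a within-arm test shows significant improvement runs from about 1% to over 90%, driven by how much patients change for other reasons. Between-group tests of change hold at about 5% throughout. The planned ANOVA is not invalidated. The weakness lies in what the additional t-tests could be used to claim, and in the contrast that is missing.

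**What to change.** Name two contrasts as the basis for the effectiveness claims: training versus health education and taping versus health education. Estimate each as a baseline-adjusted difference with a 95% confidence interval, for VAS and AKPS, for example at three months. The planned group × time model can stay alongside, as can training versus taping for the second hypothesis. Report changes within each arm as means and standard deviations without P values, and state that they are not evidence of effectiveness.

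This needs only a change of wording before analysis and uses data that will be collected anyway. The price is that within-arm P values are no longer reported and that the claims of effect may be less favourable, since improvement shared with the education arm no longer counts.

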## Discussion

There is no consistency standard for the treatment of PFPS. According to a previous study [36], neuromuscular training exercise should be an effective treatment for PFPS patients. In this study, we will carry out an RCT of neuromuscular training exercise and taping for patients with PFPS. We believe that our study will provide evidence of the effectiveness of neuromuscular training exercise in treating PFPS. Compared with health education and taping, neuromuscular training exercise could provide more beneficial effects on alleviating the pain, ameliorating knee function, and improving the PFPS patients’ quality of life.

### Strengths and limitations

First, most previous studies focused on decreasing PFPS pain intensity. However, in this study, we also make assessment on the knee joint function. In addition, we will use several knee function movements for assessment and to determine the effect of treatment. Second, we will evaluate knee proprioception in three groups. We want to determine whether the intervention group will have better knee proprioception sense compared with the other two groups. According to another study, knee proprioception plays an important role in improving knee function [18]. Third, we will set up three groups, namely, neuromuscular training exercise, taping, and health education groups, which will make the research more rigorous and comprehensive.

Despite its strength, this study has some potential limitations. The exercise training routines may not be suitable for all participants, especially those with high pain level.

In this study, we want to determine the effectiveness of neuromuscular training exercise for PFPS. We also want to estimate which method will have more beneficial effects for PFPS patients. We hope that our study will benefit patients, researchers, and policy makers with an interest in the treatment of PFPS.

### Trial status

The study registration number is ChiCTR1800014995 and the recruitment still in progress. The recruitment may be finished in October 2018.

## Data Availability

The data and the relevant results in this study will be shared through the academic conferences and the scientific papers.

## Abbreviations

AKPS: Anterior Knee Pain Scale
PFPS: Patellofemoral pain syndrome
RCT: Randomized controlled trial
SD: Standard deviation
SF-36: Short form 36
VAS: Visual analog scales
